### Predictor variables

A systematic review has highlighted 22 predictor variables included in varying combinations by 10 preceding prediction models developed to detect incident AF in the community.^16^ In addition, a more recently published machine learning model has established six further time-varying variables (eg, change in body mass index between the latest two quarters).^19^

To capture the full potential of deep learning and this large dataset, we will broaden our search for candidate predictors to all available variables, while retaining temporal information (including all clinical assessments, hospitalised events and medications). The potential predictors may include the following:

Sociodemographic variables including age, sex, ethnicity and indices of multiple deprivation.All disease conditions during follow-up, including hospitalised diseases and procedures, such as other cardiovascular diseases, diabetes mellitus, chronic lung disease, renal disease, inflammatory disease, cancer, hypothyroidism and surgical procedures.Clinical assessments including heart rate, systolic and diastolic blood pressure, height, weight and body mass index.Medications prescribed including antihypertensives, statins, antidepressants, anxiolytics/hypnotics and antipsychotics.Lifestyle factors including smoking status and alcohol consumption.All biomarkers routinely collected during follow-up including total, high-density lipoprotein and low-density lipoprotein cholesterol, triglycerides, creatinine, C reactive protein, erythrocyte sedimentation rate.

Predictive factors will be identified using the appropriate codes. In CPRD, we will use Read codes for diagnoses, measurements (eg, systolic and diastolic values) and product codes (prodcodes) for medications. In HES APC, we will use ICD-10 codes and Office of Population Censuses and Surveys Classification of Interventions and Procedures version 4 (OPCS-4) codes. In the ONS Death Registration data file, we will use ICD-10 codes (and ICD-9 codes for the period before 2001).

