### Missing data

Missing data are expected in EHR data, and will be handled using multiple imputations according to the approaches suggested by Carpenter and Kenward, and depending on the amount of missing data.^33^ It is likely there will be misclassification of baseline characteristics, such as smoking status, cholesterol, blood pressure and weight that change over time. To account for this, we will define baseline information using only measures recorded within the last year. We will then use measures taken within the last 2–5 years and in the year after baseline as parameters in the chained imputation equations used to impute baseline covariates with ≤40% missingness. In addition, median imputation, a common approach to deal with missing values in machine learning algorithms, will be used to test the model robustness.^34^

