#### Identification and quantification of the magnitude of predictors

The proposed deep learning models can extract informative risk factors from EHR data. Specifically, a risk factor selection strategy proposed by Huang *et al*^57^ will be adapted to identify informative risk factors. The model will provide weights of the identified risk factors to help understand the significance of risk factors at different risk levels. The impact of the number of risk factors on AF risk prediction performance will be assessed through the curves of both AUC and prediction accuracy plotted against the number of risk factors. Some predictors, such as body mass index, blood pressure, frequency of visits and strength of the prescribed medication, may change over time. The incremental prognostic values of including these variable trajectories will be explored, and the impact on predictive accuracy will be assessed.

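### Read literally, the missing-data rule skips values 12–24 months old, treats an older adult height as missing, and draws on data from after baseline

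*Protocol article*

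**What the plan says.** The Missing data section of the protocol article sets three linked rules. For baseline values, "we will define baseline information using only measures recorded within the last year". For imputation, "We will then use measures taken within the last 2–5 years and in the year after baseline as parameters in the chained imputation equations", and these equations are "used to impute baseline covariates with ≤40% missingness". The reason given for the short window is that features such as smoking, cholesterol, blood pressure and weight vary with time, so old values may misclassify the patient. Multiple imputation is to be applied "depending on the amount of missing data", and median imputation "will be used to test the model robustness".

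Baseline is 1 January 2009 (Outcome ascertainment), and the extract starts on 2 January 1998. The Predictor variables section lists height among the clinical assessments and includes "All biomarkers routinely collected during follow-up including total, high-density lipoprotein and low-density lipoprotein cholesterol, triglycerides, creatinine, C reactive protein, erythrocyte sedimentation rate". Risk may be predicted at 1, 3 and 6 months and at 1, 5 and 10 years (Development and external validation of model).

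**The concern.** The rule has three weaknesses as worded.

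- **Gap.** The first window ends one year before baseline and the second, taken literally, begins two years before. The values between them are more recent than those the equations use, and would normally say more about the missing baseline value.
- **Scope.** The reason concerns features that vary with time, but the rule is worded for baseline information in general. Adult height is stable, and body mass index is calculated from it. A height measured three years earlier would be replaced by an estimate.
- **Limit.** A one-year window combined with a 40% ceiling is demanding in a population of all linkage-eligible adults. A covariate not measured in at least 60% of them during one year loses chained imputation.

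The same sentence also lets measures from the year after baseline inform baseline predictors. That year covers the 1-, 3-, 6- and 12-month horizons, so some of these values may be recorded after AF has begun, and none would exist when the model is used.

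At stake are the quality of the imputed predictors and the ability to quantify less frequently tested risk markers, which is one of the study's aims.

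**Working it through.** **Inputs from the article:** baseline window of 1 year; auxiliary windows of 2–5 years before and 1 year after baseline; missingness limit of 40%. The article gives no testing frequency or missingness by variable, so there is no figure of its own to reproduce here.

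**Assumption:** the mean interval between tests, T, is 1 to 5 years and the same for all patients. Two patterns bracket the timing: random (Poisson) and strictly regular.

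**Formulas**

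- No value in the last w years: exp(−w/T) if random; max(0, 1 − w/T) if regular.
- Latest value 12–24 months old: exp(−1/T) − exp(−2/T) if random; min(1, 2/T) − min(1, 1/T) if regular.

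**Interval at which the 40% limit is reached**

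- Random: exp(−1/T) ≤ 0.40 gives 1/T ≥ 0.916, so T ≤ 1.09 years.
- Regular: 1 − 1/T ≤ 0.40 gives T ≤ 1/0.6 = 1.67 years.

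| T (years) | Missing in 1 year: random / regular | Latest value 12–24 months old: random / regular | Missing in 5 years: random / regular |
|---|---|---|---|
| 1 | 37% / 0% | 23% / 0% | 1% / 0% |
| 1.5 | 51% / 33% | 25% / 33% | 4% / 0% |
| 2 | 61% / 50% | 24% / 50% | 8% / 0% |
| 3 | 72% / 67% | 20% / 33% | 19% / 0% |
| 5 | 82% / 80% | 15% / 20% | 37% / 0% |

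For example, random testing with T = 2 gives exp(−0.5) − exp(−1) = 0.607 − 0.368 = 0.239.

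**How the gap and the limit interact.** The gap affects chained imputation only for covariates that stay under the limit. For random testing that means T up to 1.09 years, where the gap share is at most 0.40 − 0.16 = 24%. For regular testing it means T up to 1.67 years, where the share is at most 40%. At T = 1 with random testing, 0.233/0.368 = 63% of the patients to be imputed have their latest value in the skipped year.

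**Height.** No rate is needed. A height dated more than a year before baseline fails the wording of the baseline definition and therefore counts as missing.

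**Post-baseline year.** The auxiliary period runs from 0 to 12 months after baseline. Four of the six listed horizons (1, 3, 6 and 12 months) end within it or at its end.

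**The case against.** Much can be said for the plan.

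- The phrase about two to five years may mean the second to the fifth year back, which would leave no gap. This is a fair reading, but the text does not settle it.
- The window rule follows directly from a sentence about time-varying features, so height may not have been meant. That is plausible, yet the rule itself names baseline information without exception.
- A reader might infer that values 12–24 months old are used nowhere. The article does not support that. The Predictor variables section keeps temporal information on all available variables, the deep learning models work on histories over time, and the section on magnitude of predictors says "The incremental prognostic values of including these variable trajectories will be explored" without confining trajectories to one year.
- A reader might also infer that most of the listed biomarkers would go unimputed. No testing rates are given, regular testing moves the threshold from 1.09 to 1.67 years, and median imputation carries no 40% limit. Median imputation is only a robustness check, however, and gives every unmeasured patient the same value.
- The treatment of covariates above 40% may be set out in a fuller document, so its absence from an article is not counted as an error here.
- The authors give a reason for the one-year definition. Replacing it with five-year carry-forward would trade missingness for staleness and would not be a plain correction.

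These points narrow the concern to the wording of the windows, the scope of the rule and the post-baseline inputs. They do not remove it.

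**Conclusion.** The point holds within the missing-data rule. Taken literally, the rule omits the year from 12 to 24 months before baseline from both windows. Under random testing every 1–5 years on average, that year holds the latest value of about 15–25% of patients; under regular testing the share runs from 0% to 50%. An adult height older than a year would be imputed. Covariates tested less often than about every 1.1 years (random) to 1.7 years (regular) would lose chained imputation. All these shares rest on assumed testing rates common to all patients, so which biomarkers are affected cannot be said from the article.

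The use of post-baseline values is stated outright and needs no assumption. The article does not support a claim that the one-year baseline definition is wrong or that the comparison between models is thereby invalid.

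**What to change.** Make three changes to the Missing data section:

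1. Define the auxiliary window as all values from 1 to 5 years before baseline, so that it meets the baseline window without a gap.
2. For height, use any earlier adult value.
3. Impute from pre-baseline data only, dropping the year after baseline from the equations.

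Keep the one-year definition as primary. Add a sensitivity analysis that takes the last value within 5 years, with time since measurement and a measured/not-measured indicator as inputs, so that covariates above 40% missing in one year are not lost. With random testing every 3 years, for example, missingness falls from 72% to 19%.

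The extract reaches back to 1998, so earlier values exist for patients registered long enough before 2009. The cost is rewording, some extra preprocessing and one more analysis. Some values in that sensitivity analysis will be older, which the time-since-measurement input allows the model to discount.

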### Outcome ascertainment

The outcome of interest is first diagnosed AF or AFl after baseline (1 January 2009). We have included AFl as an outcome since it has similar clinical relevance, including thromboembolic risk and anticoagulation guidelines, as AF.^1^ These will be identified using Read codes and SNOMED CT in CPRD datasets. For HES APC events and underlying cause of death variable in the ONS Death Registration data file, the 10th revision of the International Statistical Classification of Diseases and Related Health Problems (ICD-10) codes will be used. Misclassified data can lead to systematic prediction errors and accuracy of data may vary over time.^29^ CPRD has converted older ICD codes to the newer version, increasing confidence in their validity. Nonetheless, to verify data accuracy, we will check the data accuracy by year and include the year of AF diagnosis in the prediction models to assess their impact.

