Finally, Transformers have become state of the art in natural language processing,^53 54^ and we will apply an adaption for EHR, BEHRT (BERT [Bidirectional Encoder Representations from Transformers] for EHR), which was originally developed in CPRD.^55^ This model’s structure, depicting each diagnosis code as a word, with each visit as a sentence and the entire medical history as a document, facilitates multihead self-attention, positional encoding and masked language model for EHR. BEHRT can define a representation incorporating information on the diseases afflicting a patient, the positional interactions of diseases and sequence of events, with the age of a patient linked to each visit to give a sense of time between diagnoses.^55^ This representation can then be used for a number of tasks including disease prediction.

Preprocessed patient-level data in CPRD-GOLD will be randomly split into an 80:20 ratio to create training and testing samples. The split ratio is not a significant factor, given the volume of the sample size. The model parameters and dropout rate will be chosen through a grid search and 10-fold cross-validation will be used (ie, 10% of the training data will be randomly selected as the cross-validation set).

While the outcome is binary, instead of just predicting 0 or 1 for a patient (new AF or not), the probability of that patient developing AF by different time points over months (1, 3, 6) and years (1, 5, 10) may be predicted. The probability of developing AF at each time point could be plotted to give an understanding of evolving risk of AF. The clinical risk prediction performance of the deep learning models will be compared against a range of classic machine learning techniques and traditional statistical predictive modelling methods including support vector machine, random forest, naïve Bayes and Cox proportional hazards model. Discrimination (Harrell’s c-statistic and AUC) and calibration metrics will be supplemented with positive and negative predictive values, precision, recall and area under precision-recall curve for all models.

The CPRD-AURUM dataset will then externally validate the model performance to assess generalisability. It has been shown that a lack of external validation has hampered the implementation of previous machine learning models in routine clinical practice.^56^

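### Missing baseline predictors are imputed from measurements taken in the year after baseline, so test-set and validation inputs may hold information unavailable at prediction, mainly for horizons up to 1 year

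*Protocol article*

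**What the plan says.** Four places in the protocol article bear on this.

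- **Outcome ascertainment** fixes time zero: "The outcome of interest is first diagnosed AF or AFl after baseline (1 January 2009").
- **Missing data** first sets the observed baseline: "we will define baseline information using only measures recorded within the last year". It then sets the imputation rule: besides measures from a window of two to five years before, it uses those taken "in the year after baseline as parameters in the chained imputation equations used to impute baseline covariates", for covariates with at most 40% of values missing. Median imputation is added only as a robustness test.
- **Development and external validation of model** gives the horizons: "the probability of that patient developing AF by different time points over months (1, 3, 6) and years (1, 5, 10) may be predicted". It also says: "Preprocessed patient-level data in CPRD-GOLD will be randomly split into an 80:20 ratio to create training and testing samples". AURUM then serves as external validation.
- **Ethics and dissemination** describes the intended use, a tool in general practice that flags patients at high risk of future AF.

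**The concern.** A prediction model has to be scored on inputs that exist when the prediction is made. Under the stated rule, a patient with no blood pressure, weight or cholesterol in the year before baseline gets a baseline value that depends partly on what was measured during the following year. If AF was diagnosed in that year, the later measure may reflect the disease, its work-up or its treatment, and the imputed baseline value then carries a trace of the outcome.

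Two of the study's aims are exposed. First, discrimination in the GOLD test set and in AURUM could look better than any practice could achieve, and if both datasets were imputed this way, external validation would not reveal it. Second, the aim of identifying and weighting risk markers could credit a variable for a change that followed diagnosis.

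**Working it through.** **The plan's own figure.** The plan gives no figure for this point. Its sample size does not depend on imputation: 200 / [(0.95 − 1) × ln(1 − 0.01/0.95)] = 377 996, as stated, and the fix leaves it unchanged.

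**Step 1: overlap of dates.** The imputation year runs from baseline to 12 months, and every outcome window also starts at baseline. The share of the window covered is min(1, 1 year / horizon).

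| Horizon | Share of outcome window inside the imputation year | After the fix |
|---|---|---|
| 1, 3, 6 months; 1 year | 100% | 0% |
| 5 years | 1/5 = 20% | 0% |
| 10 years | 1/10 = 10% | 0% |

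This step uses only the documents.

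**Step 2: possible size, on assumed inputs.** Only the 40% ceiling comes from the documents. The following are assumed: a genuine score with AUC 0.80; five covariates with no true association; correlation r = 0.7 between the baseline and later value; a later measure available for every patient with a missing value; a shift of s = 0.5 or 1.0 SD in a fraction f of cases; and an imputation model that omits the outcome.

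The mean displacement of an imputed covariate in cases is δ = (missing share) × r × s × f. Taking all variances as about 1:

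- AUC of one null covariate = Φ(δ/√2)
- Separation of the genuine score: d = √2 × Φ⁻¹(0.80) = 1.190, so d² = 1.417
- Combined AUC = Φ(√[(d² + 5δ²)/2])

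| Missing | f | s | δ | Combined AUC | Lift |
|---|---|---|---|---|---|
| 40% | 1 | 1.0 | 0.28 | Φ(√[(1.417 + 0.392)/2]) = 0.829 | 0.029 |
| 40% | 1 | 0.5 | 0.14 | Φ(√[(1.417 + 0.098)/2]) = 0.808 | 0.008 |
| 40% | 0.5 | 1.0 | 0.14 | 0.808 | 0.008 |
| 40% | 0.5 | 0.5 | 0.07 | Φ(√[(1.417 + 0.0245)/2]) = 0.802 | 0.002 |
| 40% | 0.1 | 1.0 | 0.028 | Φ(√[(1.417 + 0.0039)/2]) = 0.8003 | 0.0003 |
| 20% | 1 | 1.0 | 0.14 | 0.808 | 0.008 |
| 20% | 1 | 0.5 | 0.07 | 0.802 | 0.002 |

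Simulation under the same assumptions agrees. At 40% missing the lift is about 0.01–0.03 with all cases shifted, about 0.002–0.007 with half shifted, and under 0.001 with 10% shifted. A single null covariate, all cases shifted, reaches Φ(0.14/√2) = 0.54 to Φ(0.28/√2) = 0.58.

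**Step 3: a covariate that truly predicts.** A second simulation (also assumed: 1 million patients, log-odds 0.5 per SD, 1-year incidence about 0.76%, correlation 0.7 with both the earlier and the later measure, 40% missing, outcome omitted, all cases shifted) compares imputation sources.

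| Shift in cases | Fully observed | Earlier measures only | Earlier and later measures |
|---|---|---|---|
| 0 | 0.636 | 0.608 | 0.615 |
| 0.25 SD | 0.635 | 0.610 | 0.631 |
| 0.5 SD | 0.637 | 0.613 | 0.644 |
| 1.0 SD | 0.638 | 0.610 | 0.669 |

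From 0.5 SD the imputed covariate discriminates better than the complete data, which is a sign of leakage.

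**Step 4: dependence on the imputation model.** If the outcome is included in the imputation equations, the shift in cases is absorbed: the null covariates return to an AUC of 0.50 and the lift is essentially zero. Missing data does not say whether the outcome is included. Including it when imputing test or validation records would itself be leakage.

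**The case against.** The strongest defence is that later measures, and even the outcome, are accepted auxiliaries in multiple imputation when the target is an association. They could also be defended for fitting a model on training data. That stands, but the rule draws no line between fitting and scoring, and scoring is where the problem lies.

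Other limits also stand:

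- **Reach.** Only imputed values are affected, only in covariates within the 40% ceiling, and only for patients with a later measure. The ceiling is an eligibility limit and not expected missingness. Measures taken before diagnosis carry no post-diagnosis shift. The short horizons are listed as ones that may be predicted.
- **Models exposed.** The Transformer is described as using diagnosis codes and age, and the sequence representation as using diagnoses, procedures and medications. How far imputed measurements enter these models is not stated.
- **Partial check.** Median imputation uses no patient's own later values. It is secondary, however, and does not replace the main analysis.

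Three stronger readings are tempting, and the document does not support them. A reader might infer that GOLD test and AURUM performance is certainly inflated because both are imputed this way. In fact the article does not say how either is imputed: the preprocessing steps described before the split concern coding, and Software lists preprocessing and imputation as separate items. A reader might also infer that markers will look predictive only because they changed after diagnosis; Step 4 shows that this depends on an unstated choice. Finally, a reader might see measures from 12 to 24 months before baseline as left unused. The stated two-to-five-year window can equally mean the second to the fifth year, so no gap is established.

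**Conclusion.** The point holds as a defect in a stated rule. The imputation year overlaps every outcome window and covers the four shortest completely, and nothing in the text restricts the later measures to the training data or to dates before AF. Reported performance may therefore be inflated, mainly at horizons up to 1 year, and the imputed inputs could not be reproduced in practice even if AF left the later measures unchanged.

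The overlap is certain; the inflation is conditional. A lift of 0.01–0.03 on an AUC of 0.80 needs 40% missingness, five responsive covariates, a 0.5–1.0 SD shift in every case and an imputation model without the outcome. Less extreme assumptions bring it to a few thousandths or less, and at 5 and 10 years it is likely to be small. The documents give neither the shift, nor the share of cases affected, nor the actual missingness.

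**What to change.** In Missing data, for developing and evaluating the prediction model, remove the post-baseline year from the imputation equations and state that:

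1. imputation uses only data recorded on or before the prediction date;
2. the imputation model is fitted in the GOLD training sample, in a form that does not need the outcome when applied; and
3. that model is used unchanged in the GOLD test set and in AURUM.

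If post-baseline measures are kept for the separate risk-marker association aim, report that analysis separately and do not take performance figures from it.

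The change costs a sentence or two and a date filter. The downside is slightly less precise imputation for patients with no earlier measures.
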